#### 2.5.2. Impact on Family/Caregiver

The PedsQL^TM^ FIM serves as the main parent-reported outcome measurement instrument of the ResQ Family study and is assessed at baseline as well as in the follow-up survey [27,28]. Other measurement instruments such as the Parenting Stress Index or the Caregiver Impact Questionnaire were not available in all required languages, were not caregiver-specific (e.g., SF-6D, EQ5D-5L or PROMIS), were disease-specific for bronchiolitis (Impact of Bronchiolitis Hospitalization Questionnaire) or were not yet validated (e.g., ad hoc 38 item-questionnaire developed by Díez-Gandía et al.) and, therefore, not used or in a modified form only [22,23,31,32,33,34,35]. The PedsQL^TM^ FIM consists of 36 items and was designed to measure the impact of paediatric acute and chronic health conditions on parents and the family with a recall period of one month [27,28,36]. Six parental self-reported dimensions are covered: physical, emotional, social and cognitive functioning, communication and worry [27]. The module also comprises items on parent-reported family daily activities and family relationships [27]. Reliability and validity were demonstrated in populations of chronically diseased children with, for example, cerebral palsy and birth defects (and their parents/caregivers) and were also successfully tested in a community sample [27,37]. The PedsQL^TM^ FIM was validated in all official languages of the four participating countries (Swedish, German, French, Italian) and allowed the calculation of a sum score [27].

Further self-developed items based on questions from Díez-Gandía and colleagues about parental worry or concern with regard to the child’s RSV symptoms were added [22]. To ensure the target group-specific relevance and completeness of the questionnaire, an expert interview with a mother of an infant recently hospitalised for RSV was conducted. Based on her feedback and insights from previous projects, further important aspects of parents’ personal feelings during and after the hospital stay were incorporated [38,39]. As a result, questions on the possibility to be present and interactive with the child receiving intensive care, loss of work productivity and additional barriers as well as parental health literacy and support were added to the survey. Three disease-independent screening questions additionally assess the general health literacy of parents/caregivers [40]. To investigate other possible unmet needs, feelings or coping strategies in relation to the RSV infection of their child and/or the hospitalisation, parents or caregiver were asked about their personal experiences in an open question.

A summary of all measurement instruments and measurement time points can be found in Table 1.

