## 2. Materials and Methods

### 2.1. Study Population and Design

The ResQ Family study runs from December 2021 until June 2024. Data are collected between September 2022 and May 2023, corresponding to a typical RSV season duration in countries of the northern hemisphere. The project was designed as a multi-country observational study in which parents and caregivers of children hospitalised for RSV were invited to share their experiences via an online questionnaire.

Ensuring geographical distribution across Europe (Northern, Central and Southern Europe), participants living in Germany, France, Italy and Sweden are enrolled in the study. All parents and caregivers whose children (i) are under 24 months of age, (ii) were diagnosed with RSV either by a confirmed test (e.g., ELISA/IFT/PCR from nasal secretion, sputum or throat swab) or a doctor’s diagnosis based on typical symptoms during the RSV season, (iii) were hospitalised no more than four weeks ago (calculated from the day of hospital admission to the day the questionnaire was completed) for at least 12 h due to the respective RSV infection are included in the study.

After completion of the baseline survey, study participants have the opportunity to either end with an anonymous one-time attendance or provide their e-mail address for follow-up participation six weeks later, examining the lasting impact (on the family) after (the child’s) hospitalisation due to RSV.

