### 2.3. Recruitment of Study Participants

Parents and caregivers can be approached during hospital stay, at or shortly after discharge of their child hospitalised for RSV. However, conducting the survey has to take place within four weeks following the first day the child was hospitalised. This time frame was defined taking into account the average length of stay of RSV-infected children in Europe (~2.7 days) as well as the underlying study conditions intending to ensure the recruitment of a maximum number of participants, while avoiding potential recall bias [26].

Participants are mainly recruited by receiving the link to the online survey via social media and newsletter channels of the European Foundation for the Care of Newborn Infants (EFCNI) and their network. In addition, parent organisations, healthcare professionals in hospitals, professional healthcare societies—especially those included in the ESAB and PEG—as well as further networks in Germany, France, Italy and Sweden are encouraged to support the promotion of the study. They are asked to either directly engage in in-person recruitment of possible participants by distributing study-specific printout materials to affected families or to spread the survey online via their network(s).

For this purpose, a multilingual recruitment toolkit was prepared and professionally designed. The toolkit provides an overview of the project communication and survey recruitment strategies in general and includes ready-to-use elements such as graphics and text templates for social media (Facebook, LinkedIn, Instagram, Twitter), mailings, and newsletter communication, as well as templates for printout materials (postcard, flyer/leaflet). To ensure suitability and comprehensibility for the target group, all recruitment and information material was developed and, subsequently, translated in collaboration with a skilled communications team as well as native-speaking parents and medical experts of all four participating countries.

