### 2.4. Data Collection

Data for the baseline survey were collected via a self-report online questionnaire of 84 single- and multiple-choice closed questions and one open question. Besides socio-demographics of the participating parent or caregiver and the RSV-infected child, details of the child’s comorbidities as well as the child’s symptoms during RSV infection and hospitalisation are recorded. To assess the impact of the disease on HRQoL of affected families the standardised and caregiver-specific instrument PedsQL^TM^ Family Impact Module (PedsQL^TM^ FIM) as well as further self-designed questions based on existing instruments and literature in the respective field are used [27,28]. Completing the questionnaire requires approximately 20 min in total.

To evaluate changes over time, parents and caregivers who consented for future contact were invited by e-mail to take part in a follow-up six weeks after the baseline survey. A re-query of the PedsQL^TM^ FIM, further single- and multiple-choice closed questions and one open question give participants the opportunity to add more information about persistent symptoms or recovery, possible barriers and the long-term impact of the child’s RSV infection on the family in general. The time required to answer the total of 23 questions in the follow-up survey is estimated at 5–10 min.

All questions of the baseline and follow-up survey were initially set up in English, serving as a master version for the respective country languages. With the help of native speaking parent representatives and health care professionals of the PEG, questions which were not already part of the validated PedsQL^TM^ FIM were then translated into German, French, Italian and Swedish, ascertaining (linguistic) comprehensibility and accessibility to all study participants. To guarantee the expertise of both parents and doctors, each language was reviewed by at least one parent representative and one medical expert fluent in the corresponding language. By using a translation editor, all final language versions were incorporated into SurveyMonkey, an online survey tool which fulfils the requirements of the General Data Protection Regulation (GDPR) [29,30]. After the final set-up, native speakers pre-tested the questionnaire in all four languages.

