### 2.6. Statistical Analysis

The statistical evaluation will include descriptive, correlation and analytical analyses.

To measure the general impact of an RSV infection with hospitalisation on the HRQoL of affected parents and caregivers, sum scores of the PedsQL^TM^ FIM are compared to results from a community sample study [37]. Correlation analyses will be conducted between parental/caregiver quality of life and severity of the infant’s RSV infection, parental health literacy and supporting factors, work productivity (loss) and socio-demographic characteristics [21]. If variables are proven to be normally distributed, an independent sample t-test will be used; otherwise, a non-parametric alternative. A change over the observation period (t0—baseline survey until t1—follow-up study) in variables measured at both time points (see Table 1) will be calculated applying paired t-tests or by means of a non-parametric alternative (pre-post effects). With the help of multiple linear and logistic regression, it is anticipated to assess key determinates (potential stressors and preventive factors) associated with the HRQoL of affected parents and caregivers as main outcome parameter cross-sectionally and over time. The final models will be adjusted for relevant confounders such as socio-economic factors, RSV prophylaxis, comorbidities, prematurity or symptom status. Stratified and/or subgroup analysis (e.g., confirmed diagnosis vs. doctor’s diagnosis) will be performed to estimate subpopulations.

All statistical analyses will be performed using the statistical software R (R Core Team (2022), URL https://www.R-project.org, accessed on 10 March 2023) or SPSS (IBM SPSS Statistics for Windows, V.27–0, IBM Corp, Armonk, New York, NY, USA) with a significance level set at 5%. The evaluation of the open questions will be carried out by means of a structuring content analysis and with the support of an evaluation software (e.g., MAXQDA) [41,42].

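### The FIM looks back one month, but baseline can be completed from about 12 hours to 28 days after admission, so t0 scores and t0–t1 changes pool very different mixes of pre- and post-admission time

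*Protocol article*

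**What the plan says.** Section 2.5.2 of the protocol article makes the PedsQL FIM the main parent-reported outcome at both surveys and describes it as measuring the "impact of paediatric acute and chronic health conditions on parents and the family with a recall period of one month".

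Section 2.3 sets when baseline may be answered: "Parents and caregivers can be approached during hospital stay, at or shortly after discharge of their child hospitalised for RSV", with the limit that "conducting the survey has to take place within four weeks following the first day the child was hospitalised". Section 2.1 defines the eligibility interval as "calculated from the day of hospital admission to the day the questionnaire was completed" and requires a stay of at least 12 hours. Section 2.3 justifies the four-week limit by average length of stay (about 2.7 days), recruitment and recall bias. It does not mention the instrument's own recall period.

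For follow-up, section 2.4 says that consenting parents were "invited by e-mail to take part in a follow-up six weeks after the baseline survey". The anchor is the baseline survey, not the admission.

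In section 2.6, FIM sum scores are compared with a community sample. Change from t0 to t1 "will be calculated applying paired t-tests or by means of a non-parametric alternative (pre-post effects"). Linear and logistic regressions are adjusted for an open list of confounders. Time from admission to completion is not among the named confounders or the example stratum. It is also absent from the variables in Table 1 and from the limitations in the Discussion.

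**The concern.** A parent who answers on the ward is asked about a month that lay almost entirely before the admission. A parent who answers on day 28 is asked about a month made up almost entirely of the stay and the time after discharge. Both answers enter the analysis as the same t0.

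Three results are exposed:

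- **Hypothesis (a).** The t0 level is compared with a community sample. Answers that mostly describe life before admission should pull the t0 mean towards ordinary levels.
- **Change over time.** The paired test treats t0 as one occasion. For an early responder it is largely a pre-admission measure; for a late responder it is largely a post-discharge measure.
- **Hypothesis (b).** If completion day is related to severity, part of the severity association could reflect when parents answered.

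**Working it through.** The article states no sample size, effect size or expected score, so there is no figure of its own to reproduce. The check is arithmetic on the recall windows.

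**Inputs.** Recall R is one month (section 2.5.2), taken as 30 days with 28 as a check. Completion day d runs from 0.5 (12-hour minimum stay, section 2.1) to 28 (sections 2.1 and 2.3). Average stay is 2.7 days (section 2.3). Follow-up is 42 days after baseline (section 2.4).

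**Formulas.**

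- t0 window = [d − R, d]
- pre-admission share of t0 = (R − d)/R
- t1 window = [d + 42 − R, d + 42]

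| Day d | Pre-admission share, R = 30 | In hospital (2.7-day stay) | After discharge | Pre-admission share, R = 28 | t1 window, R = 30 |
|---|---|---|---|---|---|
| 0.5 | 29.5/30 = 98% | 2% | 0% | 98% | 12.5 to 42.5 |
| 2.7 | 27.3/30 = 91% | 9% | 0% | 90% | 14.7 to 44.7 |
| 7 | 23/30 = 77% | 9% | 14% | 75% | 19 to 49 |
| 14 | 16/30 = 53% | 9% | 38% | 50% | 26 to 56 |
| 21 | 9/30 = 30% | 9% | 61% | 25% | 33 to 63 |
| 28 | 2/30 = 7% | 9% | 84% | 0% | 40 to 70 |

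**Three things follow.**

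1. The t0 mix varies almost over its full range.
2. The t1 window always starts after admission (d + 12 > 0), so it holds no pre-admission time. Any pre-admission time in the change score comes from t0.
3. The gap between the two windows is 42 − R, that is 12 days (R = 30) or 14 days (R = 28), so they never overlap.

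**Illustration of possible size.** The values here are assumed, not taken from the article. Higher scores mean better quality of life, and each answer is the day-weighted mean over 30 days.

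- *Faster recovery:* 80 usually, 50 from 3 days before admission to discharge on day 2.7, then a linear return to 80 by day 14.
- *Slower recovery:* 80 usually, 50 from day −4 to day 7, then linear to 78 on day 28 and to 80 on day 60.

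| Day d | Faster: t0 | Faster: change | Slower: t0 | Slower: change |
|---|---|---|---|---|
| 0.5 | 76.5 | +3.4 | 75.5 | −2.6 |
| 7 | 70.8 | +9.2 | 69.0 | +7.7 |
| 14 | 68.6 | +11.4 | 63.1 | +15.6 |
| 28 | 69.6 | +10.4 | 59.8 | +19.8 |

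Within each scenario the disease course is identical in every row; only the survey day differs. Under both curves the earliest responders show the least impact and the smallest change. How much completion day matters after the first week depends on the curve: about 2 points of change under the faster one (+9.2 to +11.4), about 12 under the slower one (+7.7 to +19.8).

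**The case against.** The strongest reply is that the article does not exclude timing. Its confounder list is introduced by examples, and a full analysis plan may well add days since admission. That stands: one cannot say that no analysis will use it. But an added regression covariate would not alter the paired test as described, and the mismatch between recall period and survey window is set by the design stated here.

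Second, the four-week limit has a merit. With a one-month recall it keeps the admission inside every t0 window, so no baseline score misses the event. This also stands. The fault is the varying mix, not a missed exposure.

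Third, the size is unproven. The article gives no distribution of completion days, recruitment is mainly by online link, and nothing shows that many parents answer in the first days. This is correct and limits the claim.

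Several stronger readings are tempting but unsupported:

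- A reader might infer that t1 also mixes in time before the illness. Its window never reaches back to admission.
- A reader might call the early part of the t0 window healthy time. The documents support only pre-admission, because symptoms precede admission by an interval not given.
- A reader might conclude that the change can reverse sign. That occurs only under an assumed slow recovery, and only for completion in about the first two days.
- A reader might take confounding by recruitment channel or country as shown. The documents contain no evidence on it.
- A reader might want follow-up scheduled from admission. With t1 on day 42 and baseline on day 28, the windows [−2, 28] and [12, 42] would share 28 − 12 = 16 days.

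**Conclusion.** The point holds in a limited form. From the article's own figures, the pre-admission share of the t0 recall window runs from about 98% to 7% (98% to 0% with a 28-day recall), and the t1 window opens anywhere from about day 12 to day 40 after admission. The community comparison and the paired test, as described, pool these mixes. Early responders will tend to dilute the measured impact and change.

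That direction assumes that pre-admission life was better than the acute period and that answers reflect the whole recall month. The size cannot be determined from the article; it depends on the recovery course and on when parents actually answered. In an observational survey that already disclaims causal effects, an average over respondents remains usable as description. This is a cheap improvement, not a condition for the analysis to go ahead.

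**What to change.** 1. Keep the exact number of days from admission to completion for every respondent, not only a yes/no eligibility check, and report the distribution.
2. Add this variable, as a linear plus a flexible term (quadratic or spline), to the t0 and change regressions.
3. Supplement the paired test with the change estimated by completion timing, for example up to day 7 against later. Show the community comparison in the same split.
4. For the severity association, give results with and without the timing term. Longer stays may delay completion, so timing may lie downstream of severity and adjustment is not automatically the right primary model.
5. Leave follow-up six weeks after baseline, so that the recall windows stay separate.
6. State the varying mix in the limitations.

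The cost is two or three degrees of freedom per model and some wording. The eligibility rule already defines the interval, so no new question should be needed if the underlying dates were stored. The article plans data collection only until May 2023, so the remedy lies in the analysis and reporting and needs no change of design.

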### 2.6. Statistical Analysis

The statistical evaluation will include descriptive, correlation and analytical analyses.

To measure the general impact of an RSV infection with hospitalisation on the HRQoL of affected parents and caregivers, sum scores of the PedsQL^TM^ FIM are compared to results from a community sample study [37]. Correlation analyses will be conducted between parental/caregiver quality of life and severity of the infant’s RSV infection, parental health literacy and supporting factors, work productivity (loss) and socio-demographic characteristics [21]. If variables are proven to be normally distributed, an independent sample t-test will be used; otherwise, a non-parametric alternative. A change over the observation period (t0—baseline survey until t1—follow-up study) in variables measured at both time points (see Table 1) will be calculated applying paired t-tests or by means of a non-parametric alternative (pre-post effects). With the help of multiple linear and logistic regression, it is anticipated to assess key determinates (potential stressors and preventive factors) associated with the HRQoL of affected parents and caregivers as main outcome parameter cross-sectionally and over time. The final models will be adjusted for relevant confounders such as socio-economic factors, RSV prophylaxis, comorbidities, prematurity or symptom status. Stratified and/or subgroup analysis (e.g., confirmed diagnosis vs. doctor’s diagnosis) will be performed to estimate subpopulations.

All statistical analyses will be performed using the statistical software R (R Core Team (2022), URL https://www.R-project.org, accessed on 10 March 2023) or SPSS (IBM SPSS Statistics for Windows, V.27–0, IBM Corp, Armonk, New York, NY, USA) with a significance level set at 5%. The evaluation of the open questions will be carried out by means of a structuring content analysis and with the support of an evaluation software (e.g., MAXQDA) [41,42].

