(a)An RSV infection with hospitalisation has an impact on the health-related quality of life (HRQoL) of affected parents and caregivers;(b)The severity of an RSV infection with hospitalisation is associated with health-related quality of life (HRQoL) of parents and caregivers (over time);(c)Socio-economic status, parental health literacy and support modify the association between the severity of an RSV infection with hospitalisation and health-related quality of life (HRQoL) of parents and caregivers.

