However, some limitations need to be depicted. The study has an observational family cohort study design and is, therefore, not able to reveal causal relationships. Direct effects cannot be estimated as the study lacks a control group. Nevertheless, and provided that sufficient participation in the follow-up study six weeks later is achieved, the study group is confident to be able to inform about changes of the HRQoL of affected families over time and in different European healthcare settings. Recruitment of participants is primarily conducted via social media channels and, thereby, follows a voluntary response procedure, possibly addressing a certain target group only to a certain extent. This could have a potential impact on the representativeness of the results and may lead to sampling bias. As this survey is a self-reported questionnaire, potential self-report biases due to factors such as social desirability can occur [43]. Another problem might arise in the diagnosis of children who are not officially tested for RSV. This could lead to an inclusion of children with a suspected but not confirmed RSV infection. Lastly, since the study exclusively considers hospitalised RSV patients, results cannot be fully transferred to outpatient cases.

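### The comparison with a published community sample cannot measure the impact stated in hypothesis (a) and should be presented as an external benchmark

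*Protocol article*

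**What the plan says.** The Introduction lists three main hypotheses without ranking them. Hypothesis (a) is worded as an effect: "An RSV infection with hospitalisation has an impact on the health-related quality of life (HRQoL) of affected parents and caregivers".

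Section 2.6 introduces the matching analysis with its aim, "To measure the general impact of an RSV infection with hospitalisation on the HRQoL of affected parents and caregivers", and then states the method: sum scores of the PedsQL "FIM are compared to results from a community sample study [37"]. No other analysis is tied to that aim.

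Adjustment appears later in the same section, for the regression models of determinants: "The final models will be adjusted for relevant confounders such as socio-economic factors, RSV prophylaxis, comorbidities, prematurity or symptom status". Section 2.6 also provides for group tests ("If variables are proven to be normally distributed, an independent sample t-test will be used; otherwise, a non-parametric alternative") and gives the threshold for all analyses as "with a significance level set at 5" per cent.

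The Discussion says that the observational design cannot reveal causal relationships. It adds "Direct effects cannot be estimated as the study lacks a control group", and concedes that voluntary response may bias the sample.

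**The concern.** The Methods assign a causal question to a contrast that the Discussion says cannot answer it. A lower mean in the study than in the reference could be reported as the impact of RSV hospitalisation when some or all of it comes from who the respondents are, where they live, which language version they completed, or how they were reached. According to Section 2.7 the findings will go to policy makers, parent organisations and the public, so the wording of this conclusion matters. More recruitment does not help: it narrows the sampling error but leaves any background gap as it was, so a test becomes more likely to call that gap significant.

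**Working it through.** **Step 1: what the design can separate.** Write the observed mean difference between study and reference as D = I + B + error. I is the effect of RSV hospitalisation, and B is any difference that would exist without it. To separate I from B, the study needs at least one of the following:

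- *Unexposed families measured alongside.* There are none. The inclusion criteria in Section 2.1 require a child hospitalised for RSV, so everyone is exposed.
- *A score from before the illness.* There is none. Section 2.3 places the baseline survey during the stay or afterwards, within four weeks of admission.
- *Adjustment of the external contrast.* None is described. The confounders in Section 2.6 belong to models fitted within the study sample, and those models contain no unexposed family. They cannot estimate I.

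The contrast therefore identifies only I + B. Possible contributors to B that can be read from the article are child age (all under 24 months), four countries with four language versions, and voluntary response mainly through social media. How the reference sample stands on these cannot be seen from the article, so neither the size nor the sign of B is known.

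**Step 2: what a test would do with B alone.** The article gives no sample size, SD or reference mean, so there is no planned figure to reproduce. The calculation below is an illustration.

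Inputs:
- Significance level 0.05, from Section 2.6; two-sided is assumed.
- True impact I = 0, equal SDs, gap d = B in SD units, and sample sizes n (study) and m (reference): all assumed.

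Formulas, with Phi the standard normal distribution function:
- SE = sqrt(1/n + 1/m), in SD units
- P(significant) = Phi(d/SE − 1.96) + Phi(−d/SE − 1.96)

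For d = 0.2:
- 100 versus 100: SE = sqrt(0.01 + 0.01) = 0.141; d/SE = 1.414; Phi(−0.546) plus a negligible second term = 0.293.
- 400 versus 300: SE = sqrt(0.0025 + 0.00333) = 0.0764; d/SE = 2.619; Phi(0.659) = 0.745.
- 300 versus 900: SE = sqrt(0.00333 + 0.00111) = 0.0667; d/SE = 3.00; Phi(1.04) = 0.851.

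Probability of a significant result when RSV has no effect:

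| n versus m (assumed) | d = 0.1 | d = 0.2 | d = 0.3 |
|---|---|---|---|
| 100 versus 100 | 0.109 | 0.293 | 0.564 |
| 400 versus 300 | 0.258 | 0.745 | 0.975 |
| 300 versus 900 | 0.323 | 0.851 | 0.994 |
| 800 versus 900 | 0.539 | 0.984 | 1.000 |

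With d = 0 the value is 0.05 in every row. Over this grid the result runs from 11% to about 100%.

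**Step 3: what an interval adds.** The 95% half-width is 1.96 × SE: 0.15 SD at 400 versus 300 and 0.23 SD at 100 versus 300. This covers sampling error only. To rule out a background gap of 0.2 SD, the observed difference would have to exceed 0.20 + 0.15 = 0.35 SD in the first case and 0.20 + 0.23 = 0.43 SD in the second.

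**The case against.** **The article does not say that the comparison is unadjusted.** This stands. It is a condensed account, and the full plan may standardise. The supportable statement is that no adjustment is described. Standardising to published characteristics would reduce some of B, but it would create neither a control group nor a pre-illness score.

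**No test is attached to this comparison.** This also stands. The t-test sentence follows the one on correlation analyses, and its link to the community comparison is an inference. A mean set beside a published mean would fit the wording equally well. The rejection rates above are therefore conditional on testing. A reader might infer that the plan will declare background differences significant, or that the test can hardly fail. The documents do not support that, because they give no sample sizes and no evidence that a gap exists.

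**The authors disclose the limits.** They do, for causality, the missing control group and sampling bias. But the Discussion does not connect these limits to the community comparison, and hypothesis (a) and Section 2.6 keep the language of impact.

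**The sum score might seem biased by construction.** Section 2.5.2 says of the module: "Six parental self-reported dimensions are covered: physical, emotional, social and cognitive functioning, communication and worry". A reader might infer that community parents must score better on worry and communication, so that part of the difference is guaranteed. The documents do not show who was in the community sample or which scales it reported. Section 2.5.2 also describes the module as built to capture the effect of a child's illness, so greater worry after a hospital stay is arguably part of the construct.

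**The planned change over time might seem a better basis for the claim.** It compares families with themselves, but from a baseline during or after the illness. It mixes recovery, infant maturation and selective opt-in to follow-up. The severity gradient answers hypothesis (b). Both are uncontrolled as well.

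**Conclusion.** The point holds as a mismatch between the stated aim and what the named analysis can deliver. The comparison can show whether caregivers in the study differ from a published reference; it cannot show that RSV hospitalisation caused the difference. This follows from the article's own text and needs no assumption about numbers.

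The size of a possible error does rest on assumptions: two-sided testing at 5%, equal SDs, no true effect, and assumed sample sizes and gaps. For a gap of 0.2 SD the chance of a spurious significant result is about 29%, 75% or 85% in the three worked cases. These figures show how a test would behave if a gap existed, not that one does.

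Hypothesis (a) should not be read as the single primary hypothesis, since the article ranks none of the three. The matter deserves correction because it changes what may be concluded, but it leaves the data collection and the other analyses untouched.

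**What to change.** In Section 2.6:

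- Describe the comparison as a benchmark against an external reference, and drop the aim of measuring impact.
- Report the mean difference with a 95% confidence interval, and draw no impact conclusion from it.
- Standardise or restrict the study sample on characteristics published for the reference sample, only where the two overlap. The study has no children of 24 months or older, so do not extrapolate beyond that age.
- If the reference reports subscales, show those differences beside the sum score.
- Report the change from baseline to follow-up and the severity gradient as supporting evidence, stating that they too are uncontrolled and do not carry an impact claim.

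In the Introduction, reword hypothesis (a) to say that the quality of life of affected parents and caregivers differs from a community reference. This agrees with the Discussion, where one sentence should link the missing control group and the voluntary sampling to this comparison.

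The cost is some rewording, one standardised estimate if the published reference allows it, and a more modest conclusion on hypothesis (a). No new data are needed. Standardisation may leave country, language version and recruitment route uncorrected, and the report should say so.
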